### Statistical analysis

The analysis of the primary and secondary endpoints will be performed according to the intention-to-treat principle (ITT). There will be no interim analysis. The ITT analysis population will include all randomized participants who have a valid baseline and at least one valid post baseline wound assessment (examination). For the ITT analysis population, participants will be assigned to the treatment group based on the randomization schedule, regardless of the treatment actually received. As a secondary approach a per protocol (PP) analysis will be performed excluding patients with any serious protocol deviations and changes of wound treatment. The rates of wound closure will be compared using Fisher’s exact test and time to complete closure will be compared using the Log-rank test. Safety data will be presented on an ‘as treated’ basis where patients will be grouped according to the exact wound treatment performed. Safety and secondary endpoints will be analyzed using conventional univariate testing. For the analysis of the primary efficacy endpoint missing values will be incorporated as censored values.

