### Power calculation

The superiority hypothesis is tested in parallel with two different outcomes for the rate of wound closure and the time to wound closure in a fixed maximum treatment period of 16 weeks. The method of Bonferroni-Holm will be used for the adjustment of the α-error for parallel confirmatory testing of both primary endpoints. This means that after testing for both endpoints the smaller P value has to be <0.025 while the other has to be <0.05 for statistical significance. The sample size calculation is based primarily on the difference between wound closure rates in both treatment arms. The expected difference of the wound closure rates is based on information extracted from published previous studies. Armstrong and Lavery [16] described a rate of complete wound closure within 56% of patients with NPWT and within 39% of patients in the corresponding control group. Blume [17] showed a rate of complete wound closure within 43% of patients treated with NPWT and 29% of patients in the control group. For the present study success rates for achieving of the primary endpoint of 45% for NPWT and 30% in the control group are assumed, resulting in an absolute difference of at least 15% in the rate of complete wound closure results. Based on a type one error of α = 0.05 and a type two error of β = 0.2 (corresponding to a power of 80%) a total sample size of 162 patients per group (324 in total) is needed to prove the primary endpoint (wound closure rate).

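### 162 per group does not give the stated 80% power for the closure rate: Fisher's exact test inside the Bonferroni-Holm pair gives between 67.4% and 76.5%

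*Protocol article*

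**What the plan says.** The Power calculation section gives the planning rates: "success rates for achieving of the primary endpoint of 45% for NPWT and 30% in the control group are assumed". It then sets the error rates, "Based on a type one error of α = 0.05 and a type two error of β = 0.2", and concludes that "a total sample size of 162 patients per group (324 in total) is needed to prove the primary endpoint (wound closure rate". It does not say whether α is one- or two-sided, or which formula was used.

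The same section makes the rate one of two primary endpoints tested together: "The method of Bonferroni-Holm will be used for the adjustment of the α-error for parallel confirmatory testing of both primary endpoints". The thresholds follow: "the smaller P value has to be <0.025 while the other has to be <0.05 for statistical significance".

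The Statistical analysis section names the tests: "The rates of wound closure will be compared using Fisher’s exact test and time to complete closure will be compared using the Log-rank test". It limits the analysis set to randomised patients with a valid baseline and at least one valid later wound examination, and treats missing values of the primary endpoint as censored. Neither section gives a loss rate or an inflation of the sample size.

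**The concern.** The sample size and the analysis it is meant to support do not belong together. The calculation uses the full α of 0.05, while the adjoining text asks for 0.025 on the smaller P value. The planned test is Fisher's exact test, which is conservative and needs more patients than a normal-approximation formula without continuity correction.

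The test, thresholds, rates and sample size all stand in the article, so the power figure can be checked without an analysis plan. At stake is the only operating characteristic that the protocol states: the chance of detecting a true 15-point difference in closure. If the figure is too high, the chance of missing such a difference is larger than the 20% that readers are told.

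**Working it through.** **Inputs.** Rates 0.45 and 0.30, α = 0.05, power 80%, 162 per group, Holm thresholds 0.025 and 0.05 (Power calculation). Fisher's exact test and log-rank test (Statistical analysis). 1:1 allocation (Methods/Design). 112 days of treatment (Primary and secondary endpoints).

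**Step 1: reproduce 162.** With z(0.975) = 1.960 and z(0.80) = 0.8416:

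- Pooled formula: n = [1.960·√(2 × 0.375 × 0.625) + 0.8416·√(0.45 × 0.55 + 0.30 × 0.70)]² / 0.15² = (1.3419 + 0.5693)² / 0.0225 = 162.3.
- Arcsine formula: h = arccos(0.10) − arccos(0.40) = 1.4706 − 1.1593 = 0.3114; n = 2 × (1.960 + 0.8416)² / h² = 161.9.
- Unpooled formula: 159.6.

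The alternatives tried do not give 162:

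| Calculation | n per group |
|---|---|
| one-sided 0.05 | 128 (141 with continuity correction) |
| two-sided 0.05 with continuity correction | 176 |
| two-sided 0.025 | 197 (210 with continuity correction) |

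So 162 corresponds to a single two-sided test at the full 0.05 without continuity correction. The z-test power at 162 is 79.9%. Two-sidedness is an inference from this match.

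**Step 2: power of the planned test.** Sum over all 2×2 tables:

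Power(α) = Σₓ Σᵧ Bin(x; 162, 0.45) · Bin(y; 162, 0.30) · 1{Fisher P(x, y) ≤ α}

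- α = 0.05: 76.5%
- α = 0.025: 67.4%

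**Step 3: bounds under Holm.** The rate is declared significant if Fisher P < 0.025, or if Fisher P < 0.05 and log-rank P < 0.025. The first condition alone gives the floor, 67.4%. Fisher P < 0.05 is always necessary, which gives the ceiling, 76.5%. Both bounds hold for any healing-time distribution with 45% and 30% closed at day 112. If the threshold sentence were read as requiring both tests to succeed, the ceiling would still apply but the floor would not.

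**Step 4: position between the bounds.** This needs a healing-time model, which the article does not give. Simulation with 162 per group and no loss, with Weibull times calibrated to 45% and 30% at day 112 (10,000 trials per row, Monte Carlo standard error about 0.4 points):

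| Shape, NPWT / control | Pattern | Power for the rate under Holm |
|---|---|---|
| 1 / 1 | proportional hazards | 72.7% |
| 2 / 2 | proportional hazards | 72.3% |
| 1 / 1.5, 1 / 2, 1 / 3 | NPWT closures relatively earlier | 75.5%, 76.1%, 76.0% |
| 1.5 / 1, 2 / 1 | NPWT closures relatively later | 68.0%, 68.0% |

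A separate run of 20,000 trials with exponential times gave 72.5%.

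**Step 5: sample size for 80% on the rate, no loss.** Fisher at 0.05 needs 174 per group (80.2%). Fisher at 0.025 needs 211 (80.3%), which holds whatever the log-rank result. Under Holm with proportional hazards the number is about 192.

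**Step 6: loss, as an assumed range only.** Under proportional hazards, losses of 5%, 10% and 15% give about 70%, 67% and 64% if lost patients are excluded. They give about 71%, 70% and 68% if lost patients stay in the set as not closed.

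**The case against.** The strongest reply is that little is wrong with the design itself. Holm is a valid procedure, type I error is controlled, and no estimate is biased. Fisher's conservatism on its own costs 79.9 − 76.5 = 3.4 points; the rest comes from Holm and depends on a healing-time pattern that the article does not specify. All of this stands. It limits the point to the power statement, but does not rescue that statement, because even the ceiling is below 80%.

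The article does not support three stronger readings that a reader might infer.

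- *That power is 72-73% at best.* That figure assumes proportional hazards, which the article does not state. If NPWT closures come relatively earlier, power approaches 76.5%.
- *That power is really 67% once patients are lost.* No loss rate is given, and a condensed article may leave a recruitment margin to the full protocol. Treating every loss as an exclusion also departs from the Statistical analysis section, which removes only patients without a valid baseline or any later examination and censors other missing values.
- *That replacing Holm by a fixed sequence, log-rank first, recovers the shortfall at almost no cost.* This too rests on proportional hazards. With NPWT closures relatively later (shapes 1.5 / 1 and 2 / 1), simulated power for both tests to pass in sequence was 71.8% and 65.5%, against about 76% for Fisher alone at 0.05. In the second case the sequence does no better for the rate than Holm. It would also make the rate unclaimable whenever the log-rank test failed, although the trial is sized on the rate.

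That a payer would misread a null result is conjecture, and the point does not need it.

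**Conclusion.** The power statement is wrong as written. On the protocol's own rates, sample size, test and thresholds, power for the closure rate is at least 67.4% and at most 76.5% with no loss, so the type II error is 23.5% to 32.6% and not 20%. Under proportional hazards it is about 27-28%.

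The range rests on two-sided testing, ordinary Holm rejection rules, full evaluability and the assumed 45% and 30%. It does not depend on a healing-time model; the 72-73% figure does. Loss lowers every figure by an amount that the article does not allow one to fix.

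**What to change.** In the Power calculation section:

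1. State the method behind 162 per group, including sidedness. If the match above is right, this is a two-sided normal-approximation test at 0.05 without continuity correction or multiplicity adjustment.
2. Replace the 80% claim by the power of the planned analysis: 67.4% to 76.5% for the closure rate with Fisher's exact test under Bonferroni-Holm, before losses, and about 72-73% if proportional hazards are assumed.

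This costs a few sentences and a less favourable figure; no procedure, endpoint or patient number has to change. If the sponsor wishes to keep an 80% claim under the present analysis, the sample size has to rise: to about 192 per group under proportional hazards, or 211 per group to guarantee it, before losses. A different multiplicity procedure is an optional choice, and its gain or loss should be shown across several healing-time patterns before it is adopted.

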## Discussion

### Trial preparation and organization

Within a European tender the study was initiated by the statutory health insurance in Germany. A consortium of 19 statutory health insurance funds including the Federal Association of Local Health Insurance Funds (AOK-Bundesverband), the Association of Substitute Health Funds (vdek-Verband der Ersatzkassen e.V.), and the Sickness Fund for Miners and Seamen (Knappschaft) including the Maritime Health Insurance Fund (See-Krankenkasse). These statutory health funds are the central contact for the study project and all associated health insurance funds provide integrated care contracts for ambulant NPWT of study patients. The Institute for Research in Operative Medicine (German: Institut für Forschung in der Operativen Medizin (IFOM) of the University of Witten/Herdecke is an independent scientific institute that is responsible for the scientific conception, analysis and reporting of the study. Furthermore, IFOM monitors the compliance with regulatory and quality requirements. The University of Witten/Herdecke has taken over the sponsorship of the trial. A management company, Gesundheitsforen Leipzig (GFL), is responsible for the logistics, the financial aspects and the study site selection, as well as patient recruitment for the study. The study database is provided and hosted by the GFL. The trial is funded by the participating statutory health insurance companies and the manufacturers Kinetic Concepts Incorporated (KCI) and Smith & Nephew (S&N). Both companies provide the NPWT systems in the assigned regions of Germany as well as all necessary information about the used medical devices and associated consumable supplies. Recruitment of study patients is performed in hospitals and outpatient facilities with a specific qualification for the treatment of chronic diabetic foot wounds all over Germany. A webpage provides more information about the overall study project. The website can be found using the uniform resource locator http://www.wound-care.de.

### Ensuring outpatient care of study participants with NPWT

In Germany outpatient care with NPWT is not generally reimbursed. To ensure the optimal patient-centered care and to avoid any bias, the participating health insurance companies are providing integrated care contracts for NPWT in the ambulant treatment sector. Moreover, integrated care contracts are provided for the ambulant NPWT of up to 7000 patients with acute and chronic wounds in Germany.

### Healing characteristics of chronic wounds and justification for the testing of two primary endpoints

Chronic diabetic foot wounds were chosen as the target study population because they are considered to be a fair representation of chronic wound types and also are frequently associated with the types of comorbidities observed with other types of open wounds. In chronic wounds the balance of individual physiological processes of wound healing is permanently disrupted and wound healing is extremely difficult or impossible. Regarding the healing time, stagnation within a non-healing state is observed. The treatment of chronic wounds is often characterized by prolonged or permanently insufficient applied therapeutic methods. The resumption of the physiological healing process in chronic wounds requires a longer start-up process than in the acute wound, where the physiological processes are in balance. The treatment of chronic wounds such as diabetic foot wounds is an interdisciplinary challenge. In addition to the burden on the patient, the associated health-economic costs can be enormous. According to Kaplan-Meier curves in the study of Blume [17] complete wound closure using NPWT was achieved after an average of 96 days, whereas the time for wound closure using standard therapy was not determinable. Thus, in chronic wounds the rate of achieved wound closures within a predetermined treatment time is of specific interest. This results in the definition of the primary endpoint as the number of wound closures within the maximum study treatment period of 16 weeks. In addition, a precise evaluation of the time required to reach a complete wound closure comparing the two arms of the study is of primary interest and of high economic importance.

### Definition of chronic wounds

The available literature on the definition of a chronic wound (for example expert standards and guidelines) shows a very heterogeneous picture [18] and ranges from four to eight weeks or more for minimum existence of the lesion. It was decided that patients who suffer for four weeks or longer from the continuous existence of a diabetes-associated foot lesion are suitable for participation in the present study.

### Wound closure

The FDA 2006 Guidance for Industry [19] defines complete wound closure as ‘skin closure without drainage or dressing requirements’. Wound closure can be achieved by delayed primary intention (secondary suture, skin flap or skin graft) or secondary intention according to requirements of the participant and wound in the estimation of the attending physician. Optimal care for the participant has to be ensured. Independent from type of closure, criteria for wound closure have to be reached within a maximum time frame of 112 days and wound closure has to be confirmed for a minimum of 14 consecutive days. Within each treatment arm surgical wound closure may only be performed if an adequate preparation of the wound bed (minimum 95% granulation tissue) has been achieved.

### Avoiding potential bias

Within the reports of the IQWiG and the updated systematic literature review of Peinemann and Sauerland [14] the risk of bias within the considered trials was examined using the predefined criteria shown in Table 2. All five criteria had to be met for the potential for bias to be described as low. The DiaFu- study is designed with the aim of avoiding all potential bias.

**Table 2 Tab2:** **Potential bias**

Criteria for potential bias	Explanation
RCT	The performance of a randomized controlled trial is required.
Suitable allocation to groups	A precise description of the randomization sequence generating procedure is required (such as computer-generated lists).
Allocation to groups suitably concealed	Information on how allocation to groups is blinded is required (for example centrally by telephone or using sealed opaque envelopes).
Assessment of endpoints blinded	Information on who (patient and/or researcher) assessed which endpoint under blinding conditions (without knowing the group to which the patient had been allocated) is required.
Reasons given for any data loss	The requirement is either no data loss or, if data loss is reported, identification of all patients whose data could not be fully evaluated after randomization and the reasons for this (for example patients who dropped out before the beginning of treatment or during follow-up).
Adequate ITT analysis	Evaluation using the number of randomized patients as the size of the population is required

### Ethical conduct of the study

This study is conducted in accordance with the International Conference on Harmonization (ICH) Harmonized Tripartite Guidelines for Good Clinical Practice 1996, the European Union (EU) Directive 95/46/EC on the protection of individuals with regard to the processing of personal data and on the free movement of such data as transposed into national law, the EU Medical Device Directive 93/42/EC as amended by Directive 2007/47/EC as amended into national law, the International Organization for Standardization (ISO) 14155 related to AE definitions and in the spirit of the Declaration of Helsinki concerning medical research in humans (latest edition).

### Publication of study results

Both positive and negative results of the trial will be disclosed. The results of the trial will be submitted for publication to peer-reviewed scientific journals and presented at international scientific congresses. The Principal Investigator and the Steering Committee are responsible for the primary and secondary publications and/or presentations arising from the study. All publications will maintain data protection of participant data as well as data of the participating clinical investigators. Results will be reported according to CONSORT recommendations [20].

## Trial status

Recruiting since December 2011.

Stop of recruitment estimated for 10/2014.

## Abbreviations

ADEs: Adverse device events/device-related adverse events
AEs: Adverse events
EC: Ethical committee
EU: European Union
FDA: Food and Drug Administration
G-BA: German: Gemeinsamer Bundesausschuss (English: German Federal Joint Committee)
GFL: German: Gesundheitsforen Leipzig
ICH: International Conference on Harmonization
IDF: International Diabetes Federation
IFOM: German: Institut für Forschung in der Operativen Medizin (English: Institute for Research in Operative Medicine)
IQWiG: German: Institut für Qualität und Wirtschaftlichkeit im Gesundheitswesen (English: Institute for Quality and Efficiency in Healthcare)
ISO: International Organization for Standardization
ITT: Intention-to-treat
KCI: Kinetic Concepts Incorporated
LEC: Lead ethical committee (German: Federführende Ethikkommission)
MPG: German: Medizinproduktegesetz (German Medical Device Act)
NPWT: Negative pressure wound therapy
PP: Per protocol
PRO: Patient reported outcome
QoL: Quality of life
S&N: Smith & Nephew
SAEs: Serious adverse events
TNP: Topical negative pressure
WHO: World Health Organization.
